# Two parallel, pragmatic, UK multicentre, randomised controlled trials comparing surgical options for upper compartment (vault or uterine) pelvic organ prolapse (the VUE Study): study protocol for a randomised controlled trial

**DOI:** 10.1186/s13063-016-1576-x

**Published:** 2016-09-08

**Keywords:** Uterine, Vault, Prolapse, Hysterectomy, Suspension, Symptoms, Randomised controlled trial

## Abstract

**Background:**

One in three women who have a prolapse operation will go on to have another operation, though not necessarily in the same compartment. Surgery can result in greater impairment of quality of life than the original prolapse itself (such as the development of new-onset urinary incontinence, or prolapse at a different site). Anterior and posterior prolapse surgery is most common (90 % of operations), but around 43 % of women also have a uterine (34 %) or vault (9 %) procedure at the same time. There is not enough evidence from randomised controlled trials (RCTs) to guide management of vault or uterine prolapse. The Vault or Uterine prolapse surgery Evaluation (VUE) study aims to assess the surgical management of upper compartment pelvic organ prolapse (POP) in terms of clinical effectiveness, cost-effectiveness and adverse events.

**Methods/design:**

VUE is two parallel, pragmatic, UK multicentre, RCTs (Uterine Trial and Vault Trial). Eligible for inclusion are women with vault or uterine prolapse: requiring a surgical procedure, suitable for randomisation and willing to be randomised. Randomisation will be computer-allocated separately for each trial, minimised on: requiring concomitant anterior and/or posterior POP surgery or not, concomitant incontinence surgery or not, age (under 60 years or 60 years and older) and surgeon. Participants will be randomly assigned, with equal probability to intervention or control arms in either the Uterine Trial or the Vault Trial. Uterine Trial participants will receive either a vaginal hysterectomy or a uterine preservation procedure. Vault Trial participants will receive either a vaginal sacrospinous fixation or an abdominal sacrocolpopexy. Participants will be followed up by postal questionnaires (6 months post surgery and 12 months post randomisation) and also reviewed in clinic 12 months post surgery. The primary outcome is the participant-reported Pelvic Organ Prolapse Symptom Score (POP-SS) at 12 months post randomisation.

**Discussion:**

Demonstrating the efficacy of vault and uterine prolapse surgeries is relevant not only to patients and clinicians but also to health care providers, both in the UK and globally.

**Trial registration:**

Current controlled trials ISRCTN86784244 (assigned 19 October 2012), and the first subject was randomly assigned on 1 May 2013

**Electronic supplementary material:**

The online version of this article (doi:10.1186/s13063-016-1576-x) contains supplementary material, which is available to authorized users.

## Background

The reasons for the trial (see also Additional file 1 for further background):

Gynaecologists have recognised for some time that both anatomical failure and recurrence of prolapse symptoms after surgery are common: one in three women who have a prolapse operation will go on to have another, though not necessarily in the same compartment [1]. More recently, it has also been recognised that surgery can be followed by a greater impairment of quality of life than from the original prolapse itself (e.g. the development of new-onset urinary incontinence after surgery, or prolapse at a different site). While anterior and posterior prolapse surgery is most common (90 % of operations), around 43 % of women also have a uterine (34 %) or vault (9 %) procedure at the same time. Indeed, this demonstrates that women who have a hysterectomy have around a 27 % chance of needing a subsequent vault prolapse repair.

These data are derived from the first 700 women recruited in PROSPECT (PROlapse Surgery: Pragmatic Evaluation and randomised Controlled Trials in women with anterior or posterior pelvic organ prolapse), a large HTA-funded UK randomised controlled trial (RCT) of anterior or posterior prolapse surgery with or without the use of mesh (HTA No. 07/60/18) also being undertaken by the research team. VUE is a follow-on trial in which women will be randomised to different surgical options for upper compartment prolapse (vault and uterine). This protocol sets out our plans for running VUE.

Our aim is to identify the optimal surgical procedures for women with a vault or a uterine prolapse, which will provide women with the best symptomatic cure and lowest adverse effect and reoperation rates. Given the number of prolapse procedures currently performed and the anticipated rise in the need for such surgery with an ageing population, [2] the potential cost implications for the health service are considerable. The findings will guide gynaecologists in their surgical practice and purchasers in their choice of provision of health care. The study aims to identify which procedures are not only most clinically effective but also most cost-effective.

## Summary of evidence base

Systematic reviews have demonstrated that there was not enough evidence to guide practice for women contemplating surgery for their vault or uterine prolapse [3, 4]. The trials for vault surgery were individually too small to be conclusive and, hence, guide practice. Three RCTs broadly addressed hysterectomy versus uterine preservation approaches, but differences in the approaches and techniques used, and the outcome measures reported, precluded any useful meta-analysis or conclusions. Thus, there is no reliable evidence to guide women and their gynaecologists in choosing the best surgical cure for vault or uterine prolapse.

## Implications for proposed project

There is insufficient information about any of the surgical options to guide management of vault or uterine prolapse in women. We have identified, from PROSPECT and Health Episode Statistics (HES) data that around a third of women with prolapse have a hysterectomy for uterine prolapse. At least 25 % (HES data [2]) and 27 % (PROSPECT data) of these women go on to have a subsequent vault prolapse procedure. The evidence base for treating either of these groups of women is clearly inadequate, with very little evidence regarding subjective prolapse symptoms, effect on quality of life, cost-effectiveness and safety.

This study will fulfil the research need identified by the Cochrane review [3] and the Interventional Procedures (IP) review [4] for adequately powered RCTs of the surgical options for women having vault or uterine prolapse surgery. It will comprise two of the largest, rigorous and independent RCTs comparing traditional prolapse operations with each other. We will take into account the different clinical characteristics of women having concomitant procedures such as anterior or posterior repair, or incontinence surgery, and identify confounding factors which may predict outcomes.

## Choice of comparators

### Uterine Trial

The two options for uterine prolapse concern removal or retention of the uterus. There are a number of surgical approaches to both options (vaginal, open abdominal, laparoscopic, robotic laparoscopic) and for pragmatic reasons we intend to allow surgeons to choose the techniques which they routinely use, within certain broad categories. This will allow the maximum number of gynaecologists to recruit to VUE.

### Vault Trial

The two broad approaches to vault suspension are vaginal or abdominal. There is a general clinical opinion that the vaginal approach has a higher recurrence rate but it is simpler to perform and has less morbidity, but there is no good evidence to underpin this. Again there are different techniques to both approaches, and we intend to allow gynaecologists to use their preferred operations, again within certain broad categories.

These comparators will be further debated within the clinical and research community through the Research Committee of the British Society of Urogynaecology (BSUG) with the aim that VUE will be adopted by the Society.

## Principal objectives

The two parallel trials will compare:*Uterine Trial*: in women having uterine prolapse surgery, the effects of removal of the uterus versus uterine preservation*Vault Trial*: in women having vault prolapse surgery, the effects of a vaginal vault suspension versus an abdominal vault suspension

The primary objective is to determine the optimal surgical management for women with upper compartment (vault or uterine) pelvic organ prolapse in terms of clinical effectiveness, cost-effectiveness and adverse events (AEs).

## Secondary objectives

To determine the differential effects on other outcomes such as urinary, sexual and bowel function, quality of life, general health, need for secondary surgery and adverse effectsTo identify possible effect modifiers (e.g. concomitant procedures, age, complex prolapse types)

## Methods/design

VUE comprises two parallel, multicentre, RCTs of surgery for women with vault or uterine prolapse. The trial flow diagram is presented in Fig. 1.

**Fig. 1 Fig1:**
[figure not shown]
Flow diagram of study design and schedule. POP-SS (Pelvic Organ Prolapse Symptom Score), POP-Q (Pelvic Organ Prolapse Quantification)

### Women considered for trial entry

The study will involve women who are having prolapse surgery for vault or uterine prolapse. Two parallel but separate trials will be conducted.A.*Uterine Trial* for women with a uterine prolapse:Experimental: uterine preservation (vaginal sacrospinous fixation of uterus with sutures or mesh, *or* open abdominal or laparoscopic sacrohysteropexy with a mesh bridge).Control (standard): vaginal hysterectomy, with a prespecified vault suspension technique using sutures or mesh if necessaryB.*Vault Trial* for women with a vault prolapse;Control (standard): vaginal sacrospinous fixation (with sutures or mesh or a mesh kit).Experimental: abdominal sacrocolpopexy (open abdominal or laparoscopic, with a mesh bridge)

Permitted concomitant procedures are:Anterior and/or posterior repair,Enterocele repair andContinence procedure (e.g. mid-urethral sling, colposuspension)

The operations selected for VUE are described in more detail in Additional file 1.

Divergence from prespecified choices will be documented with reasons. All other operative variables will be described using standardised data collection forms. The exact surgical options will be agreed and standardised by consensus with the Research Committee of BSUG before the trial begins.

### Problems with compliance

We feel that the noncompliance rate amongst gynaecologists will be low because we will recruit gynaecologists who are uncertain about which operation to choose for their patients, and who are motivated to help with research to establish the answer.

We found that the women recruited to PROSPECT were particularly well-motivated to participate in the study: only 8.1 % declined to be recruited, 86.9 % have attended for outpatient review and there is, so far, a 94.9 % response rate to the primary outcome at 12 months.

Inclusion criteria:Women with vault or uterine prolapse requiring a surgical procedureWomen who are suitable for randomisation (gynaecologist’s view, i.e. not meeting exclusion criteria)Women who are willing to be randomised (woman’s view)

Exclusion criteria (women who are unwilling, unable or unsuitable to be randomised):Previous subtotal hysterectomyPrevious cervical amputation (Manchester repair)Potential future pregnanciesComorbidity necessitating particular approach (e.g. fibroids, previous abdominal surgery (scarring/adhesions))Comorbidity precluding randomisation (e.g. poor anaesthetic risk)Obesity precluding abdominal approach (except if two vaginal approaches are feasible)Colpocleisis (vaginal closure operation)

### Identification and enrolment of potential participants

All women listed for vault or uterine prolapse surgery will be identified by their treating gynaecologist and a dedicated research nurse in each centre over the 2-year recruitment period. A log will be maintained of all women meeting the eligibility criterion (listed for vault or uterine prolapse surgery), describing reasons if they do not enter the study. Every woman will be allocated a unique Study Number.

Local procedures at the participating hospitals are different and the timing and mode of approach to women and the consent process will vary to accommodate both the variability at the sites and the needs of the women. Each eligible woman will be given or sent a Patient Information Leaflet describing the study, a customised Surgical Information Sheet, a baseline questionnaire and a Consent Form. Each woman will have the opportunity to discuss the study with her gynaecologist. Women will also have the opportunity to discuss all aspects of the study with the local clinical team (staff at preadmission clinics and ward staff while admitted), the research nurse, family and friends and, if appropriate, with their GP before admission. Women may make a decision to participate during a consultation with their gynaecologist, during a visit to hospital (e.g. when they attend a clinic appointment, when they attend for preassessment or when they are admitted for surgery), or alternatively at home. If the woman agrees to be contacted at home (recorded on the Surgical Assessment Form), she may receive a telephone call from the local research nurse to discuss any queries. Women who decide to participate following telephone counselling can either send their completed documents (Consent Form and baseline questionnaire) through the post to the local team at their treating hospital or bring it with them if they are returning to hospital for another consultation or surgery.

Each woman will be asked for her signed informed consent to be randomised and followed up after her prolapse surgery by postal questionnaires and an examination in the Gynaecology Outpatient Department. The Patient Information Leaflet and the Consent Form will all refer to the possibility of long-term follow-up and being contacted about other prolapse research if the women are willing.

Each GP will be informed about each of their patients who participate in the study. Hospital staff will be informed about the study by the principal investigator (PI) and the research nurse so that they can answer queries from participants and their relatives.

All women who enter the study will be assigned a Study Number, complete a baseline questionnaire including measurement of prolapse, bowel, urinary, vaginal and sexual symptoms, and have an objective prolapse assessment (Pelvic Organ Prolapse Quantification (POP-Q) [5]) carried out by the gynaecologist or the research nurse. Women who consent will be randomised into one of the trial arms appropriate for her type of prolapse. Randomisation will be carried out as close to the time of surgery as is practical, taking into account the hospital routines and timely need for setting up the operating theatre.

All consenting women will be asked to complete the follow-up questionnaires at 6 and 12 months at home. They will also have a review appointment with their gynaecologist at 12 months to evaluate the results of surgery using the POP-Q examination and identify problems or need for other treatment. This amounts to considerably more postoperative surveillance than is available routinely in the NHS, and should ensure that all women receive optimum care.

### Number of centres involved

We aim to recruit women from approximately 40 centres, many of which also participated in PROSPECT.

### Methods to protect against sources of bias

#### Randomisation (avoiding selection bias)

When contact details, essential baseline information and confirmation of signed consent are entered into the Internet-based VUE database, the local researcher will be able to randomise the woman in the trial for which she is eligible (see flow diagram, Fig. 1). Randomisation will be carried out as close to the time of surgery as is practical taking into account the hospital routines and time needed for setting up the operating theatre.

Every woman will be logged with the Study Office and given a unique Study Number. Randomisation will utilise the existing proven remote automated computer randomisation application at the study administrative centre in the Centre for Healthcare Randomised Trials (CHaRT, a fully registered UK CRC Clinical Trials Unit) in the Health Services Research Unit, University of Aberdeen. This randomisation application will be available as an Internet-based service.

Randomisation will be computer-allocated separately for each trial and minimised on:need for a concomitant anterior and/or posterior POP operation or noneneed for a concomitant incontinence procedure (e.g. tension-free vaginal tape (TVT)) or notage (under 60 years or 60 and older), andsurgeon

The choice of operations available to randomised women will be determined by whether they are having vault or uterine prolapse surgery. The basic criterion for joining the study is that the gynaecologist must be uncertain regarding the best operative technique for the majority of patients, and they must be competent to perform the operations to be compared (i.e. be ‘beyond’ the learning curve).

### Ensuring standardisation of intervention and outcome measurement (avoiding performance bias)

Both specialist urogynaecologists and general gynaecologists will be eligible for recruiting and randomising women, thus extending the generalisability of the trial and the future transfer of skills. All gynaecologists will be proficient in performing the POP-Q [5] method of objective quantification of prolapse descent used pre and postoperatively.

All gynaecologists will complete a Surgical Standardisation Form to provide details of their preferred operative techniques. The gynaecological surgeons who have agreed to participate in the study have extensive experience and training in prolapse surgery. Any additional training required will be conducted by the clinical grant applicants and will be directed towards ensuring standardisation of their existing techniques and outcome measures.

The research nurses and the surgeons will complete a Recruitment Officer Case Report Form (ROCRF) (developed for PROSPECT and to be adapted for VUE) at the time of surgery to ensure a complete record of all surgical techniques and materials used and any intraoperative difficulties or complications. The research nurses in each centre will ensure completeness and accuracy of data entry using remote data capture via a study web-based portal at the Study Office in Aberdeen, authored and managed by the UK CRC-registered Clinical Trials Unit in Aberdeen (CHaRT).

As this is a pragmatic trial, postoperative care will be according to local centre practice but clinical and resource-use data will be recorded.

### Loss to follow-up (attrition bias)

We have used a conservative estimate of 15 % loss to follow-up in the power calculations. We will take very active measures to minimise such loss, such as telephoning the women, using retention incentives and checks with their GPs. In addition we will obtain consent from the women to enable us to access centrally-held NHS data, for example, via the NHS Strategic Tracing Service in England and Wales, and using Community Health Index (CHI) numbers from the Information Services Division in Scotland. We have extensive experience of using such strategies and measures and have received ethics approval to do so in previous studies.

### Other sources of bias (detection bias)

Group allocation will be concealed from the woman and the ward staff if clinically possible, although blinding in theatre is not possible given that this is a surgical trial. However, we do not feel that it is necessary or ethical to perform sham incisions to conceal the route of surgery. Outcome assessment is largely by participant self-completed questionnaire, so avoiding interviewer bias. However, the clinical review at 12 months in the Outpatients Department (secondary outcome) will be conducted by staff blinded to allocation by performing the POP-Q examination, without knowledge of the actual procedure performed when possible. Participants will undergo an objective vaginal POP-Q assessment before the group allocation is revealed. Women and research staff will not be explicitly informed of which operation was randomly selected, although examination may reveal which operation was actually carried out, and women will be told if they wish to know.

Research staff who are blinded to allocation will conduct the data collection, data entry and analysis using Study Numbers only to identify women and questionnaires. All women will be actively followed up, with analysis based on the intention-to-treat principle. All analyses will be clearly predefined to avoid bias, and will be rehearsed in PROSPECT to ensure compatibility of results.

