### Subsequent arrangements

#### Informing key people

Following formal trial entry:

The Study Office will inform the woman’s GP (by letter enclosing information about VUE and Study Office contact details).

The local research nurse will:File the hospital copy of the Consent Form in the hospital notes along with information about VUE and the POP-Q measurementsInform the ward and theatre staff as appropriate of the woman’s entry to the study and details of the intervention allocation (theatre only)Use the VUE Internet database to enter data regarding the participant, including data required to complete randomisation; and intraoperative and postoperative information abstracted from local medical recordsReturn all study documentation to the Study Office in Aberdeen after database entry of essential data

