### Case Report Forms (CRFs)

#### Baseline/hospital research nurse CRF

At baseline, the research nurse will complete a Case Report Form with the following content:

PreoperativeContact details, GP address, telephone numbersGynaecological and obstetric historyMeasurement of prolapse stage using POP-Q [5]Planned operative details

IntraoperativeIntraoperative data including date of admission and operationOperative procedures and theatre timeCatheter and vaginal pack useComplications

PostoperativePain relief, laxative use, infection, haematoma, other complicationsReturn to theatreDate of discharge

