### Data processing

Research nurses will enter locally collected data in the centres. Staff in the Study Office will work closely with local research nurses to ensure that the data are as complete and accurate as possible. Follow-up questionnaires to women will be sent from and returned to the Study Office in Aberdeen. Extensive range and consistency checks will further enhance the quality of the data.

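### The blinding statement covers all data collection and entry, but the site research nurse who records and enters the perioperative and complication data knows the allocation

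*Protocol article*

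**What the plan says.** The section on other sources of bias (detection bias) makes two general statements about staff. The first is "Research staff who are blinded to allocation will conduct the data collection, data entry and analysis using Study Numbers only". The second is "Women and research staff will not be explicitly informed of which operation was randomly selected", with the proviso that examination may reveal the operation. The same section accepts that theatre cannot be blinded. It also says the 12-month clinic review will be done by blinded staff where that is possible, with the POP-Q taken before the allocation is revealed.

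Other sections assign the work at site:

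- **Randomisation (avoiding selection bias):** "the local researcher will be able to randomise the woman in the trial for which she is eligible". Local organisation in centres lists this among the local research nurse's duties.
- **Informing key people:** the same nurse passes on "details of the intervention allocation (theatre only") and enters intraoperative and postoperative information from the medical records.
- **Ensuring standardisation of intervention and outcome measurement:** "The research nurses and the surgeons will complete a Recruitment Officer Case Report Form (ROCRF") at the time of surgery. The form covers techniques, materials and intraoperative complications.
- **Baseline/hospital research nurse CRF:** "At baseline, the research nurse will complete a Case Report Form with the following content". The content runs on to operative procedures, complications, infection, haematoma and return to theatre.
- **Data processing:** "Research nurses will enter locally collected data in the centres".

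**The concern.** Someone who has obtained the allocation, passed it to theatre and written down which operation was done is not blinded when recording that operation's complications. Using Study Numbers instead of names does not change this.

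The protocol puts adverse events in its primary objective and lists postoperative morbidity and complications as secondary outcomes. Some of these need judgement. Under the safety definitions, adverse events judged unrelated to a procedure the protocol requires are not recorded at all, apart from deaths, so a judgement about relatedness decides whether an event is counted. The local principal investigator confirms serious events. The arms differ in surgical route and in the use of mesh, and the choice-of-comparators section reports a prevailing clinical opinion that the vaginal approach to the vault carries less morbidity. Differential recording is therefore plausible. A reader relying on the blinding statement would rate these outcomes as better protected than they are.

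**Working it through.** No arithmetic applies, because the point concerns who knows what and when. The check compares the blinding statements with the duties assigned elsewhere, by data source.

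**1. Perioperative CRF data.** Table 2 has two CRF entries at surgery: clinical status and adverse events. The forms are completed by the research nurse and the surgeon. The nurse has randomised the woman and informed theatre, and the surgeon has performed the operation. The nurse then enters the data. Both collection and entry are by people who know the allocation, so the general statement is untrue for this source.

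**2. Postal questionnaires (POP-SS, EQ-5D, patient-reported symptoms).** The women complete these themselves. Data processing has follow-up questionnaires sent from and returned to the Study Office. The site nurse's knowledge does not enter into their recording, and the blinding statement can stand here if the staff who handle questionnaires do not also see the operative forms. That condition is worth stating, because sites return paper copies of operative and postoperative data to the same office.

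**3. 12-month clinic CRF data.** Table 2 has three CRF entries here: clinical status, adverse events and hospital admissions. The POP-Q has its own qualified blinding statement. However, the section on identification and enrolment says the woman is reviewed by her own gynaecologist. The article does not say whether this is the surgeon who operated, so the two descriptions need reconciling. The section on the 12-month clinical review form names nobody as completing or entering it.

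**4. Adverse events and admissions from other sources.** Table 2 also collects both by participant questionnaire at 6 and 12 months. The section on HES and ISD data uses centrally held records of operations, diagnoses and admissions to supplement and validate what participants report. These sources do not depend on the site nurse.

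**5. Complication coding.** The adverse-effects and SAE form sections name the IUGA/ICS systems but do not say who applies the codes. Unblinded coding is therefore possible but not shown.

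**6. Analysis.** Nothing in the assigned duties contradicts the statement that analysis is blinded.

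The contradiction is thus established for source 1 and for complications and adverse events that site staff record on CRFs around surgery. It is open for source 3 and absent for sources 2, 4 and 6.

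**The case against.** The best defence is that the research staff in the blinding sentence are Study Office staff. The sentence goes on to say that Study Numbers identify women and questionnaires, and the Study Office section makes that office responsible for data collection, follow-up, processing and analysis, a very similar list. The protocol also says openly that theatre cannot be blinded, and it does not hide who fills in the forms.

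This makes the narrower meaning a plausible intention, but it does not repair the text. Site research nurses are research staff, and four other sections give them collection or entry of CRF data. The disclaimer about theatre concerns the operation and does not extend to recording and entering what happened in it.

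Other parts of the defence stand. Operating time and nights in hospital leave little room for judgement. Readmission is largely a matter of fact and has two further sources. Blinding the people who record an operation is hardly feasible, so the fault is in the claim and not in the choice of recorder.

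A reader might go further and infer that every CRF outcome is unblinded, including those from the 12-month clinic, and that the same nurse enters them all. The documents do not support this: the POP-Q has its own blinding statement, and the reference to research nurses entering local data is general. Nor do they support an inference that the primary outcome is compromised by this route, or that complication rates would be distorted by any particular amount. No borderline-event rate or misclassification rate is given.

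**Conclusion.** The point holds for perioperative and complication outcomes recorded at site: they are collected and entered by staff who know the allocation, contrary to an unrestricted statement that they are not. The size is one of scope. It covers the two CRF entries at surgery in Table 2 and the complication data recorded on the hospital forms. Recording of the POP-SS, and every sample size and analysis specification, is unaffected. The 12-month POP-Q is a related inconsistency to reconcile and is not shown to be unblinded.

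The conclusion assumes that the nurse who randomises and informs theatre is the one who completes the operative form, or works closely enough with that person to share the knowledge. The article describes a single local research nurse role with all these duties, although it allows for alternative recruiters during absence. Even with a second nurse, the form itself names the operation performed and the surgeon helps to complete it. The correction is worth making because adverse events are part of the primary objective, but it changes no estimate.

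**What to change.** In the detection-bias section:

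- Limit the claim of blinded collection and entry to Study Office handling of participant questionnaires, by staff without sight of the operative forms.
- Keep the statements on blinded analysis and on the 12-month POP-Q, and reconcile the latter with the sentence giving that review to the woman's gynaecologist.
- State that site-recorded perioperative and adverse-event CRF data are collected by staff who know the allocation, and that participant-reported events and central admissions data are separate sources.

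In the adverse-effects section, have existing Study Office staff apply the IUGA/ICS complication codes from the event description, by Study Number and without the allocation or operation field, where the description does not itself disclose the operation.

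The cost is revised wording and a restricted database view. No visits, participants or procedures are added. The downside is that the stated blinding becomes less favourable, and some descriptions, such as mesh exposure, will still reveal the operation, so masked coding will be partial.
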